### Treatment conditions

#### Tobacco Status Project (TSP)

The TSP is a smoking cessation intervention implemented entirely through “secret” (Facebook’s word for entirely private) Facebook groups. All TSP participants are assigned to a Facebook group based on their TTM stage of change (precontemplation: not ready to quit in the next 6 months; contemplation: intending to quit in the next 6 months; or preparation: ready to quit in the next month and demonstrating at least one past year quit attempt).

The group-based intervention has three main features. First, evidence-based strategies have been used to design Facebook posts to be delivered each day for 90 days to intervention groups on Facebook. Posts are based on the US Clinical Practice Guidelines for smoking cessation [2] and the Transtheoretical Model (TTM) of behavior change [44], both recommending treatment be tailored to participants’ readiness to quit, and have been determined to be helpful to and likable by young adults ([name], [name], [name], [name]: Feasibility and quit rates of the “Tobacco Status Project”, submitted). Precontemplation group posts are based on Motivational Interviewing (MI), a directive patient-centered counseling intervention recommended by the Clinical Practice Guidelines [2, 45]. Posts elicit clients’ motivation and importance of changing tobacco use, problems associated with use, and using open-ended questions to elicit “change talk” (a client’s mention of desire, ability, reason, or commitment to change) through using the 5-R’s: relevance, risks, rewards, roadblocks, and repetition, shown to increase likelihood of tobacco quit attempts [46, 47]. Contemplation group posts incorporate MI and the TTM processes of self-liberation (e.g., making a commitment to quit), stimulus control (e.g., removing smoking paraphernalia from the home), and counter conditioning (e.g., engaging in alternative behaviors) are emphasized. Preparation group posts incorporate skills from cognitive behavioral therapy, found effective for long-term smoking cessation [48], as well as the TTM processes of self-liberation (e.g., making a commitment to quit), stimulus control (e.g., removing smoking paraphernalia from the home), and counter conditioning (e.g., engaging in alternative behaviors). Posts also encourage setting a quit date and making a detailed quit plan. Facebook posts include a combination of images, videos, text and polls designed to reflect the experience of young adults and all elicit a response from participants. Posts may suggest that participants use their FB or real social networks for support with alcohol or tobacco reduction. However, they are not required to share any information about substance use on social media. Figure 2 provides sample posts for each stage of change.

**Fig. 2 Fig2:**
[figure not shown]
Tobacco Status Project Sample Posts

Second, the intervention incorporates weekly “The [name] In” live sessions with a PhD level smoking cessation counselor (using FB commenting features), during which a counselor provides some limited content for discussion and participants can ask questions and get supplemental support. Content for sessions is tailored to readiness to quit tobacco and is based on Motivational Interviewing (MI) and cognitive behavioral coping skills for smoking cessation.

Third, six manualized 45-min state-of-the-art smoking cessation counseling sessions based on cognitive behavioral therapy (CBT) were adapted for social media delivery for this study. These sessions are designed to be delivered in Facebook events and events are scheduled in each group separately. In contrast to The [name] In sessions that are conversational and question and answer-based, these sessions present more material, and are designed to help participants who are motivated to quit. Thus, only participants in preparation groups are offered these CBT sessions and participants may opt to participate in the sessions at any time during the 90 days of Facebook intervention. In all groups, links to more intensive treatment in a participant’s’ area are available as needed.

Additionally, we are testing an incentive structure in which the TSP groups are randomized to one of four incentive conditions tied to engagement in the intervention: 1) daily; 2) weekly; 3) monthly; or 4) no incentive. Participants in daily, weekly, or monthly groups can earn money based on comments made to daily Facebook posts at the end of each period. At the end of the 90-day intervention, all participants in paid incentive conditions receive a gift card in the amount they have earned up to $90. This is separate from the $100 participants could earn for completing all study assessments.

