Based on this formative work, we developed the *Tobacco Status Project (TSP),* a Facebook intervention for young adult smokers combining Facebook contacts tailored to participants’ readiness to quit smoking with a 12-week cessation program consisting of 90 days of Facebook postings, weekly counseling sessions, and for those ready to quit, 7 state-of-the-art group cognitive-behavioral sessions. A feasibility trial enrolled 79 young adults who formed 7 Facebook groups [36]. Follow-up rates were 84 and 72 % at 6 and 12 months, respectively, and reported 7-day abstinence was 21 % at 6 months (9 % biochemically-verified) and 18 % at 12 months (9 % verified) ([name], [name], [name], [name]: Feasibility and quit rates of the “Tobacco Status Project”, submitted). From baseline to 12-months, there was a significant increase in the proportion prepared to quit (13 to 46 %, p < .001), 35 % reduced their cigarette consumption by 50 % or greater, and 67 % reported a 24-h quit attempt. Engagement in the intervention was high, with 92 % participation in the full 3 month intervention and 61 % commented on at least one post, with more commenting among those randomized to receive a personal monetary incentive [37]. Participants reported reading most of the Facebook posts (mean usability rating = 3.3/4) and interactions from counseling sessions (3/4), thinking about what they read (3/4) and would recommend the program to others (3.3/4). Herein, we describe a randomized controlled trial testing the efficacy of TSP against a referral control condition with 480 young adult smokers who use Facebook.

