## Methods/Design

### Overview of design

This study is a randomized controlled trial (RCT) with 480 young adults age 18 to 25 recruited through Facebook (Fig. 1). Participants are randomized to one of two conditions: (1) the Tobacco Status Project motivationally-tailored smoking cessation intervention delivered through Facebook (TSP); or (2) a control condition (referral to the Smokefree.gov website). Assessments are conducted online at baseline, 3-, 6-, and 12-months follow-up. Primary outcome is biochemically-verified 7-day point prevalence abstinence from tobacco, and secondary outcomes are reduction in cigarettes smoked per week, 24 h quit attempts, and commitment to abstinence in each time period. Within the TSP group, a monetary engagement will be tested as a moderator of engagement and abstinence.

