### Study procedure

Informed consent is obtained from all study participants in accordance with the Helsinki Declaration and approved by the UCSF Committee in Human Research (#11-06294). During the informed consent process, participants’ understanding of the information provided is assessed through a series of multiple choice questions with required responses before being able to proceed with the study. Questions are based on those used in studies with potentially vulnerable populations [41, 42]. Any wrong answers during the consent process are sent to study staff who then contact a potential participant via email or Facebook for further clarification of the consent process. Therefore, no participant will be enrolled that has not answered all consent questions correctly. Participants consenting to participate in the study are asked to verify age by sending proof through email or social media. Verified participants are emailed a baseline assessment. Those completing the baseline assessment are randomized to receive either the Tobacco Status Project (TSP) intervention of referral to the Smokefree.gov website (control).

A stratified random assignment program was developed and participants are assigned from within stratified blocks immediately after completing the baseline assessment. Participants are stratified on stage of change (precontemplation, contemplation, preparation) and smoking pattern (daily vs. non-daily), variables known to be related to outcomes and addressed by the intervention [43]. Participants in the TSP group are assigned to “secret” (private) Facebook groups based on their readiness to quit tobacco. Groups begin when there are approximately 10 participants enrolled, as that has been deemed the optimal number based on analyses of engagement in our previous work [37] ([name], [name], [name]: Smoking cessation intervention on Facebook: Which content generates the best engagement?, submitted). Participants in the control condition are given a referral to the Smokefree.gov program and are encouraged to use it as much as they would like.

Assessments occur online using the survey program Qualtrics at baseline, 3, 6, and 12 months follow-up. Participants receive their choice of gift cards in the amount of $20 per assessment, and a $20 bonus for completing all three assessments, for a total possible stipend of $100 for completing all assessments.

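### Single-stage Facebook groups are randomised to four incentive conditions with no stage stratification stated, and the planned tests ignore stage, so incentive conditions are likely to differ by chance in stage mix and CBT access

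*Protocol article*

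**What the plan says.** In the protocol article, Overview of design gives the size and the two arms: "This study is a randomized controlled trial (RCT) with 480 young adults age 18 to 25 recruited through Facebook", and "Participants are randomized to one of two conditions". Study procedure says that this individual randomisation is stratified on stage of change and on daily versus non-daily smoking, because both are known to relate to outcome. It then places TSP participants in "Facebook groups based on their readiness to quit tobacco", and adds that "Groups begin when there are approximately 10 participants enrolled".

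The section on the Tobacco Status Project describes a second randomisation, of whole groups: "the TSP groups are randomized to one of four incentive conditions tied to engagement in the intervention". The conditions are daily, weekly, monthly and no incentive. No stratification or blocking is stated for this step, and none is ruled out. The same section says that "only participants in preparation groups are offered these CBT sessions".

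Secondary analyses compares total comments by incentive condition with a Kruskal-Wallis test and a linear trend test, and abstinence by incentive condition with Pearson's chi-square. None of these has a term for stage or for Facebook group. The article gives no expected stage mix and no expected number of groups.

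**The concern.** The unit that receives an incentive condition is a group whose members share one stage. Stage is a variable that the trial itself treats as prognostic, and it also decides what treatment is offered, since CBT goes only to preparation groups. With few units per condition, chance alone can give one incentive condition mostly precontemplation groups and another several preparation groups. Stratification guards against this in the first randomisation, which has 480 units. In the second, with about 24 units, no such protection is stated, and the stated tests do not supply it at the analysis stage.

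The secondary aim is at stake. A difference in comments or abstinence between incentive conditions could partly reflect stage mix or access to CBT. A real incentive effect could also be hidden by an unfavourable mix.

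**Working it through.** The article states no number of groups per stage or per condition, so there is no figure of its own to reproduce.

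**Inputs**
- Sample size 480 (Overview of design). The allocation ratio is not stated; 1:1 is assumed, giving 240 in TSP.
- Group size about 10 (Study procedure), so 240/10 = 24 groups. As a cross-check, the Background reports that "A feasibility trial enrolled 79 young adults who formed 7 Facebook groups": 79/7 = 11.3 per group, or 240/11.3 ≈ 21 groups.
- Four incentive conditions. An equal split of 24/4 = 6 groups each is assumed.
- Share in preparation: the only figure is the pilot's 13% at baseline (Background), about 10 of 79 people. It is not a planning assumption for this trial.

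**1. Stage mix between two conditions.** Take a stage that holds 12 of the 24 groups, with no restriction on stage. The counts in the conditions are multivariate hypergeometric.
- Variance of the count in one condition: 6 × 0.5 × 0.5 × 18/23 = 1.174
- Covariance between two conditions: −6 × 6 × 0.25/23 = −0.391
- SD of the difference in shares: √(2 × 1.174 + 2 × 0.391)/6 = 1.769/6 = 0.29

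The SD is thus about 29 percentage points. Treating the two conditions as independent would give about 25 points, which is too small because the counts are negatively correlated. For a stage with 10 or 11 of 24 groups the SD is again about 29 points. Enumerating all splits gives an average gap of about 41 to 42 points between the highest and lowest of the four conditions. None of this depends on the pilot's 13%.

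**2. Number of preparation groups.** 240 × 0.13 = 31.2 people, or 3.1 groups of 10. The 95% Wilson interval for 10/79 is 7% to 22%, which is about 17 to 52 people, or 1.7 to 5.2 groups. Four groups of 10 need a share of 40/240 = 16.7%.

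**3. Three preparation groups.** The probability that the unpaid condition has none is C(18,3)/C(24,3) = 816/2024 = 0.40. Three groups cannot fill four conditions, so some condition has none whether or not allocation is blocked on stage.

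**4. Four or more preparation groups, not blocked on stage.** With k preparation groups, the probability that at least one condition has none is

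[4·C(18,k) − 6·C(12,k) + 4·C(6,k)] / C(24,k)

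| k | Calculation | Probability |
|---|---|---|
| 4 | (12240 − 2970 + 60)/10626 | 0.88 |
| 5 | (34272 − 4752 + 24)/42504 | 0.70 |
| 6 | (74256 − 5544 + 4)/134596 | 0.51 |
| 7 | (127296 − 4752)/346104 | 0.35 |

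With permuted blocks of four within stage, this probability is zero from k = 4 upward.

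**The case against.** The strongest reply is that this is a journal article. The restriction scheme of a nested randomisation for a secondary aim may well be in the full protocol, and the trial already had a stage-stratified assignment program for its first step. That stands: a reader might infer that the incentive allocation is unblocked, but the article only fails to say. The tests, however, are stated, and they leave stage out.

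A reader might also infer that some incentive condition is bound to lack a preparation group because blocking is absent. The article does not support this. It is certain only with three or fewer preparation groups, which rests on an assumed ratio and a pilot share from about 10 people; a share of about 17%, inside the pilot's interval, allows four. The Discussion adds that recruitment aims at a more diverse pool than the pilot's. And where three or fewer groups form, the cause is their number, which blocking cannot cure.

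Nor is an empty cell beyond repair. On the pilot share, about 21 of 24 groups are in precontemplation or contemplation, and incentives can be compared within those stages. What is lost is the contrast within preparation that involves the empty condition. Finally, random allocation of groups gives chance imbalance, not systematic bias. That is correct, but with about six groups per condition the imbalance in the one allocation actually drawn can be large, and stage is known in advance.

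**Conclusion.** The point holds for the secondary aim. As described, the incentive comparison sets about six single-stage groups per condition against one another with tests that ignore stage. A stage-share difference of around 29 percentage points between two conditions is one SD of chance variation. A condition without any preparation group is more likely than not at four to six such groups if allocation is not blocked on stage, and unavoidable at three or fewer.

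These figures assume 1:1 allocation, groups of 10, six groups per condition and no stage restriction. The number of preparation groups is uncertain.

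It would go too far to conclude that incentive is wholly confounded with stage or that the main result is affected. The confounding is partial: on the pilot share, CBT access differs for about 31 of 240 TSP participants. The TSP-versus-control comparison is stratified on stage and is not touched.

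**What to change.** 1. **State the allocation.** Say whether groups are allocated to incentive conditions within stage. If they already are, one sentence settles this part.
2. **If they are not, restrict what remains.** Allocate groups not yet opened within stage, in permuted blocks of four. Where a stage will form fewer than four groups, ensure that at least one is paid and one unpaid, so that a paid-versus-unpaid contrast exists in that stage.
3. **Change the analysis.** Replace the unstratified Kruskal-Wallis and chi-square tests with stage-stratified or stage-adjusted comparisons of comments and abstinence that allow for Facebook group, since groups are what was randomised. One option is a permutation test that reassigns whole groups within stage; another is a mixed model with stage as a fixed effect and group as a random effect.
4. **State the limit.** Say that a four-way incentive contrast within preparation may not be estimable, and report the number of groups by stage and incentive condition.

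The cost is a new allocation list for unopened groups and a few sentences of text. The end of a block becomes slightly predictable; this matters little if the condition is drawn once a group's members are enrolled. Adjustment loses some precision with so few groups. Recruitment is under way, so groups already opened can be handled only in the analysis.

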### Control group

Participants in the control condition, receive a referral to the National Cancer Institute’s Smokefree.gov website. This website, created by the Tobacco Control Research Branch of the National Cancer Institute, provides information and support to quit smoking for people at all stages of change. Smokefree.gov (http://www.smokefree.gov) provides free, accurate, evidence-based information and professional assistance to help support the immediate and long-term needs of people trying to quit smoking. Features of the program include a website tailored to readiness to quit smoking, a texting program, Smartphone application, online live chat, and a Facebook page. The treatment provided to control participants meets U.S. Clinical Practice Guidelines for treating nicotine dependence with adults [49].

### Measures

#### Primary outcome

The primary outcome biochemically-verified 7-day point prevalence abstinence at 3, 6, and 12 months. Participants reporting “no smoking, not even a puff” in the past 7 days will be coded as abstinent from cigarettes. At each follow-up assessment, participants reporting 7-day abstinence will be mailed a saliva cotinine test kit and asked to record two pictures: one giving a saliva sample, and another of the test result. Participants with a salivary cotinine level <11 ng/ml, indicating nonsmoking [50], will be considered confirmed nonsmokers. If participants indicate use of an electronic nicotine delivery-system to aid in smoking cessation, saliva cotinine and reported ENDS use will be recorded and reported separately from biochemically verified abstinence.

### Secondary outcomes

The following secondary outcomes will be assessed at each timepoint:**Reduction of cigarette consumption by 50 % or more (y/n)** between baseline each follow-up will be calculated from the number of cigarettes smoked in the past 7 days at each time point.**Tobacco quit attempt** (y/n). A *Follow-up Smoking Questionnaire* will assess the presence and number of 24 h quit attempts since the last assessment, used to calculate presence of at least one quit attempt in the assessment time period.**Readiness to quit tobacco** will be assessed using the *Stages of Change Questionnaire*, [44] categorizing participants into five stage categories at each timepoint (precontemplation, contemplation, preparation, action, and maintenance), and predictive of quit attempts and cessation [51]. Outcome will be measured as proportion in action or maintenance stage sof change at 3, 6, and 12 month assessments.**Abstinence goal** will be assessed with the *Thoughts About Abstinence Form, *[52]*,* categorizing goal as no goal, intermediary goal (e.g., reduced smoking), or total abstinence. Outcome will be measured as proportion endorsing a goal of abstinence at each timepoint.**Engagement in TSP** will be measured by total number of comments to Facebook study groups during the three-month intervention period.

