## Aims and hypotheses

### Main Aim: To evaluate the efficacy of the Facebook-based intervention for young adults in a randomized controlled trial

Hypotheses are:Participants receiving the intervention will have higher 7-day point prevalence abstinence at 3-, 6-, and 12-months follow-up compared to those in the control condition.Participants in the intervention condition will demonstrate greater reduction in cigarettes smoked and increased commitment to abstinence at 3-, 6-, and 12-months follow-up than those in the control condition.Participants in the intervention condition will be more likely to make a quit attempt during the 12-month study period compared to those in the control condition.

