### Inclusion criteria

Participants are required to meet the following criteria in order to be eligible for enrollment in the trial:English literate (at an 8^th^ grade reading level);age 18 to 25 years (consistent with the definition of young adulthood used by the National Survey of Drug Use and Health, and age range with the highest smoking prevalence nationally [38]);access to a digital camera that can take and send a picture (e.g., camera phone);go on Facebook “most” (≥4) days per week;≥100 cigarettes smoked in their lives; and currently smoking at least 1 cigarette per day on 3 or more days of the week. Smoking criteria are based on those used in the National Health Interview Survey and are liberal based on smoking patterns most common in young adults and to include ethnic/racial minority populations, who tend to smoke fewer cigarettes per day than Caucasians [1].

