### Secondary analyses

Mixed effects logistic and multinomial regression models for longitudinal ordinal response data to model secondary outcomes for tobacco use and across time (3, 6, 12 months): 1) reduction of cigarettes by 50 % or more (y/n), 2) tobacco quit attempt (y/n; 2 models), 3) action or maintenance stage of change (y/n); and 4) commitment to abstinence (y/n). Independent variables in all models will be treatment condition, abstinence status, and covariates identified as relevant to smoking characteristics in the literature.

To evaluate the secondary aim (effect of a monetary incentive on engagement in the TSP condition), we will test for differences in engagement and primary smoking outcome by incentive groups and the relationship between engagement and primary smoking outcome at 3 months. First, due to expected skewed distribution of the engagement variable (comments), the non-parametric Kruskal-Wallace test will examine overall differences in total number of comments made to the Facebook study group by incentive condition, with test for a linear trend in commenting by incentive frequency. Second, Pearson’s chi-square test will examine 7-day point prevalence abstinence by incentive condition. Abstinence rates will be examined by incentive group. Two sets of analyses will be conducted: one for biochemically verified abstinence, and one for reported abstinence. Finally, Mann–Whitney U tests will compare comments for those abstinent at 3months to those non-abstinent. Again, two sets of analyses will be conducted (one for biochemically-verified abstinence and one for reported abstinence).

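### Hypothesis 2 is about how much smoking falls, but only a yes/no cut at 50% is analysed; the cut misses moderate reductions in heavier smokers and is noisy in the lightest eligible ones

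*Protocol article*

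**What the plan says.** All places are in the protocol article.

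- **Aims and hypotheses, Main Aim, second hypothesis:** intervention participants "will demonstrate greater reduction in cigarettes smoked and increased commitment to abstinence at 3-, 6-, and 12-months follow-up". No threshold is given.
- **Overview of design:** "secondary outcomes are reduction in cigarettes smoked per week", again an amount without a threshold.
- **Secondary outcomes:** the variable is "Reduction of cigarette consumption by 50 % or more (y/n"), and it "will be calculated from the number of cigarettes smoked in the past 7 days at each time point". One baseline week is compared with one follow-up week.
- **Secondary analyses:** the variable that enters the mixed logistic model is "reduction of cigarettes by 50 % or more (y/n"). No model for the count is listed.
- **Inclusion criteria:** "currently smoking at least 1 cigarette per day on 3 or more days of the week", which puts the floor at about 1 × 3 = 3 cigarettes a week. Study procedure stratifies randomisation on daily versus non-daily smoking, so light smokers are an expected part of the sample.

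The abstract also uses the 50% cut. The article gives no distribution of baseline consumption, no week-to-week variability, and no power for this outcome.

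**The concern.** A single cut at half of the baseline count means different things across the range of smokers admitted. For someone at 70 a week, a fall to 50 is a substantial change but counts as failure. For someone at 3 a week, a fall to 1 counts as success, although ordinary variation between two weeks can produce it. A hypothesis about the amount of reduction is thus tested with a variable that discards most of the information on amount.

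At stake is the sensitivity of a secondary outcome in a trial that itself plans for 50% attrition at each time point. The reading of a crude percentage of reducers is also at stake, because it mixes quitters, true partial reducers and, among the lightest smokers, people who have not changed.

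**Working it through.** **The plan's own figure.** None exists for this outcome; the power calculation concerns abstinence only. The nearest figure is from the feasibility trial (Background): "35 % reduced their cigarette consumption by 50 % or greater".

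**Step 1. Unchanged smokers coded as reducers.** Let X be the baseline and Y the follow-up 7-day count, independent with the same mean. The rate is

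P(Y ≤ X/2 | X ≥ 3) = Σ over x ≥ 3 of P(X = x)·P(Y ≤ ⌊x/2⌋), divided by P(X ≥ 3).

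The distributions are assumptions. V/M is the ratio of variance to mean; 1 is Poisson.

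| Usual cigarettes per week | V/M 1 | V/M 2 | V/M 4 |
|---|---|---|---|
| 3 | 37% | 50% | 62% |
| 5 | 21% | 33% | 46% |
| 10 | 8% | 17% | 27% |
| 20 | 2% | 7% | 16% |
| 35 | 0.3% | 3% | 8% |
| 70 | 0% | 0.3% | 2% |

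Two less noisy readings at 3 a week:

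- Poisson, requiring only a non-zero baseline count: 28%.
- At most one cigarette a day, so binomial over 7 days with p = 3/7 and baseline at least 3. The probabilities of 0 to 7 are .020, .104, .235, .294, .220, .099, .025, .003. The numerator is .294 × .124 + (.220 + .099) × .359 + (.025 + .003) × .653 = .169. The denominator is .641. The rate is 26%. At 5 a week the same model gives 5%.

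**Step 2. True 25% fall, Poisson.** Proportion coded as reducers:

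- 3 a week: 54%, against 37% with no change; difference 17 points.
- 35 a week: 7%, against 0.3%; difference about 7 points.
- 70 a week: 2%, against 0%; difference about 2 points.

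The cut therefore separates changed from unchanged smokers least well among heavier smokers.

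**Step 3. Two-arm power, single time point.** Inputs: 480/2 × 0.5 = 120 completers per arm (1:1 allocation assumed), lognormal weekly means with log-SD 0.8, 5% quitters in both arms, true 25% fall in one arm. The comparator is a regression of log(count + 1) on arm and log baseline.

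| Median per week | V/M | 50% cut | Baseline-adjusted log count |
|---|---|---|---|
| 20 | 1 | 0.64 | 0.78 |
| 50 | 1 | 0.30 | 0.71 |
| 70 | 1 | 0.16 | 0.61 |
| 20 | 4 | 0.65 | 0.67 |
| 50 | 4 | 0.67 | 0.62 |
| 70 | 4 | 0.63 | 0.57 |

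The near-parity at V/M 4 comes from the log(count + 1) model, in which quitters at zero act as outliers. A log-link count model with robust errors and the baseline count as covariate had more power than the cut in every non-null setting tried. At V/M 4 with a 25% fall it gave 0.90 against 0.62 and 0.99 against 0.67 under two assumed consumption distributions. It gave 0.65 against 0.44 when the size of the change varied between people.

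With a true 40% fall, the cut and the log-count regression both reach 0.96 or more in every setting.

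**Step 4. No true effect.** With 5% quitters in both arms, the share coded as reducers was 9–21% (median 20 a week), 6–12% (50) and 5–9% (70). It was equal in the two arms apart from sampling error, and the test of the cut rejected in 4% to 7% of runs, close to nominal.

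**The case against.** **The documents do not contradict themselves.** The abstract, the outcome definition and the analysis all use the 50% cut, and the feasibility trial reported the same measure. The wording in the hypothesis and overview can be read as shorthand, and a higher proportion of reducers is a legitimate way to express greater reduction. This stands: the point is a coarse match between hypothesis and analysis, not an error.

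**A reader might infer that the trial will produce many false reducers.** The article does not support that. The number depends on the share of people near 3 to 7 a week, which is not given, and the false rate falls quickly above that range unless counts are strongly overdispersed. The floor is also a screening criterion, while the baseline count is taken later, so the 37% is not the only reasonable figure.

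**A reader might infer that the noise hides or biases the treatment effect.** It does not. The same process acts in both randomised arms, so it dilutes the contrast without favouring either, and a 40% fall is still detected.

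**A reader might set the pilot's 35% beside the 37% and call it noise.** The same section reports 18% self-reported abstinence at 12 months, and an abstainer is a reducer by definition. If the denominators match, 18/35, or about half, is reported quitting.

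**An unseen analysis plan may hold a count analysis.** It may. But the article does fix the outcome, cut, window and model, and it lists only the yes/no variable.

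**Conclusion.** The point holds in a limited form. The mismatch between a hypothesis about amount and a single dichotomised analysis can be read directly from the article and needs no assumption. Its cost is power. With a true 25% fall at 120 per arm, the cut had 0.16 to 0.67 in the settings of step 3, and a log-link count model did better wherever it was compared. For the lightest eligible smokers the cut is unreliable: about 26% to 37% of unchanged people at 3 a week are coded as reducers, and more if weekly counts are overdispersed.

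These sizes rest on assumed consumption distributions, independent weeks around a stable personal mean, 1:1 allocation and one time point. The direction is firmer than the figures. Because the outcome is secondary and the comparison remains unbiased, the weight is modest. Nothing here justifies removing the published 50% outcome.

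**What to change.** Keep the 50% outcome as published. Add to Secondary analyses a prespecified model for the past-7-day count at 3, 6 and 12 months:

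- a log-link count model, such as a negative binomial mixed model or quasi-Poisson with robust errors;
- treatment condition and assessment point, with the baseline 7-day count and the daily/non-daily stratum as covariates. Abstinence status, which that section lists for all secondary models, should be left out, since a follow-up count of zero is abstinence over that week;
- the between-arm ratio of cigarettes per week, with its confidence interval, named as the test of the reduction part of hypothesis 2.

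Report the 50% result overall and separately for daily and non-daily smokers.

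No new data are needed, because the counts are already collected at each assessment. The costs are one more secondary analysis, an effect measure less familiar than a percentage of reducers, and a dated, documented change to the plan, because recruitment is already under way.
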